### Secondary outcomes

As secondary outcomes, the impact of *Hafnia alvei* HA4597™ supplementation will be assessed towards changes in gut microbiota composition, including diversity, richness, and characterization of microbes at phylum, class, order, family, genus, and species level at baseline, and 3, 6, 9, and 12 months. Alterations in the metabolites produced by gut microbiota that have already demonstrated a protective or a deleterious effect in obesity and type 2 diabetes conditions, namely short-chain fatty acids (acetate, propionate and butyrate), trimethylamine N-oxide, indole-3-propionic acid, imidazole propionate [18–21], will also be determined at the same timepoints. Another important gut metabolite that will be assessed is ClpB, which is specifically produced by *Hafnia alvei* strain and is related to its recognized metabolic effect on appetite regulation [22]. Changes in ClpB levels will be determined before (baseline and 3 months) and after the intervention (6, 9, 12 months).

Additionally, the trial will assess the effect of supplementation on inflammatory markers, including calprotectin, zonulin, c-reactive protein, lipopolysaccharides, transforming growth factor-β, monocyte chemoattractant protein-1, interferon gamma, IL-1 β, IL-6, IL-10, and on other important metabolic outcomes, such as fasting glucose, HOMA-IR, HOMA-S, HOMA-B, and c-peptide, total cholesterol, HDL cholesterol, LDL cholesterol, VLDL cholesterol and triacylglycerides, and vitamins and minerals status (iron, calcium, zinc, copper, magnesium, vitamin B6, vitamin B12, 25-hydroxy-vitamin D) on all visits. GLP-1 and GIP will also be determined at all visits. Lastly, gastrointestinal quality of life impact will be assessed at baseline, and 3, 6, 9, and 12 months.

### Sample collection and follow-up

Eligible participants are assessed five times during the trial: at baseline (visit 1), 3 months (visit 2), 6 months (visit 3), 9 months (visit 4), and 12 months (visit 5) after bariatric surgery. Intervention (i.e. intake of probiotic or placebo) is administered 3 months after the surgery. All data is collected at Hospital CUF Tejo and the specific assessments carried out at each timepoint are identified in Table 1.

Before each visit, participants are contacted and reminded of their follow-up visits and necessary preparations via e-mails and text messages. Participants are asked to prepare for all the visits by following the instructions:Fasting for 10–12 h (allowed to drink water 4 h before the visit)Having a last meal similar to their usual habitsAvoiding alcohol and caffeine intake on the previous dayAvoiding vigorous physical exercise on the previous day

At baseline, participants respond to a questionnaire to provide sociodemographic characteristics, clinical history, and lifestyle practices. Information regarding changes in medication, supplementation and physical activity are continuously gathered throughout the trial through the electronic patient record.

At all visits, a venous blood sample is collected by a nurse/phlebotomist into sterile serum separator tubes and K_2_EDTA tubes. Subsequently, blood samples are centrifuged at 3000 rpm for 10 min at 4 °C, and aliquoted. For incretin hormones aliquot, DPP-IV inhibitor is added to plasma sample to a final concentration of 10 μL/mL of blood. Participants are also instructed to collect their own faecal samples in sterile tubes with RNAlater, provided by the research team. Subjects describe their stool frequency and consistency of evacuation using the Bristol stool scale [23]. All biological samples are stored at − 20 °C (faecal samples) or − 80 °C (plasma and serum samples) until further analysis.

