### Intervention, compliance, and adverse effects

Participants enrolled in the trial are randomly assigned to receive either probiotic or placebo. The probiotic or placebo is orally taken, twice a day, with one glass of water, approximately 5 min before both breakfast and lunch, for 90 days, between 3 and 6 months after bariatric surgery. Two capsules of the probiotic contain 5 × 10^7^ CFU of *Hafnia alvei* HA4597™, 5 mg of zinc and 20 μg of chromium. The capsules are gastro-resistant which allows the ingredients to resist stomach acidity. A placebo is used as a comparator to determine if the probiotic effect is directly related with the strain (i.e. *Hafnia alvei*). The placebo product is indistinguishable in colour, smell, and taste from the active formulation, and has the same composition but without the live bacteria.

To improve compliance, participants will receive a message every 2 weeks and a call approximately 45 days after starting the intervention to reinforce the intake of the capsules and to register any missing intake on the calendar provided by the research team.

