### Primary outcomes

The primary outcomes are the differences in the number of subjects that will lose at least 50% of excess weight, as well as the number of subjects that will have glycated haemoglobin levels lower than 5.7%, between the probiotic and placebo groups, 1 year after the surgery. The rationale behind the primary outcomes is based on previous studies that have described the effect of *Hafnia alvei* HA4597™. In the preclinical study conducted by Legrand et al. [14], the effect of *Hafnia alvei* HA4597™ supplementation was assessed in two models of obesity, in leptin deficiency *ob/ob* mice and high-fat diet (HFD)-fed obese and overweight mice. Results showed that in both models’ body weight gain was significantly lower by the end of the study (50.1% *ob/ob* and 38.1% HFD), as well as fat gain (38.3% *ob/ob* and 51.9% HFD) [14]. In addition, loss of lean mass was 126.8% lower and food intake reduced 20.8% in the *ob/ob* mice [14]. A second trial was conducted by Lucas et al. [11] using a mice model of obesity characterized by a combination of a HFD-fed obese and a genetic *ob/ob* mice which closely represents the hyperphagia and diet-induced obesity in humans (compulsive eating behaviour combined with hypercaloric diet and functional leptin resistance). The authors observed that *Hafnia alvei* HA4597™ supplementation resulted in 58.1% lower body weight gain, decreased food intake and fat mass gain, and increased lean mass preservation, resulting in an improved lean/fat mass ratio [11]. Moreover, *Hafnia alvei* HA4597™ treatment also improved metabolic outcomes, including glycemia. Basal glucose levels decreased by 1.5-fold compared to standard diet HFD-fed controls [11]. Afterwards, the efficacy of *Hafnia alvei* HA4597™ supplementation was tested in humans [15]. A randomized, placebo-controlled, double-blind trial evaluated the effect of this probiotic (5 × 10^7^ CFU of *Hafnia alvei* HA4597™) on 236 overweight men and women that were following a low-calorie diet [15]. After 12 weeks, significantly more subjects (+ 51%) lost at least 4% of their initial weight comparing to placebo [15]. Furthermore, compared to placebo, subjects in the treatment group had a significant reduction in hip circumference and glycemia, and increased feeling of fullness, which was assessed by a visual analogue scale [15].

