### Anthropometry and body composition

Height is measured to the nearest 0.1 cm with a wall stadiometer (SECA®, Hamburg, Germany), following the Directorate-General for Health protocol [24]. Participants remove their clothes, socks, and any metal objects prior to measurement of body weight and body composition (including percentage of fat mass, fat mass, fat-free mass and skeletal muscle mass) by tetrapolar bioimpedance (Inbody®, model 770, Seoul, Korea). Body mass index is also obtained by the device report and percentage of excess weight loss is calculated as: $$\frac{\mathrm{baseline\,weight}\left(\mathrm{kg}\right)-\mathrm{follow\,}-\mathrm{\,up\,weight}\,(kg)}{\mathrm{baseline\,weight}\left(\mathrm{kg}\right)-\mathrm{ideal\,weight\,for\,BMI\,}25\mathrm{\,kg}/\mathrm m^2}\times100$$ [25]. Weight and body composition is measured at all visits.

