## Statistical analysis

Statistical analysis will be performed using SPSS V.27 (IBM SPSS Statistics for Windows, IBM Corporation, Armonk, NY) and GraphPad Prism V.9 (GraphPad Software, La Jolla, CA, USA).

Participants with low compliance as defined by taking less than 80% of the pills provided by the research team and those lost to follow-up will be excluded from the per-protocol analysis but included in the intention-to-treat analysis. In addition, all participants are strongly advised not to take any probiotic supplements. Participants are asked at each visit about the intake of antibiotics and probiotics supplements, in case of intake in any period of the trial after starting the intervention, participants will also be excluded from the per-protocol analysis but will be included in the intention-to-treat analysis. In case of lost to follow-up, available data from electronic medical records will be collected.

The Kolmogorov–Smirnov test will be used to test the normality of the distribution. Descriptive statistics will be performed, and data will be presented as mean ± standard error of mean (SEM) (for normally distributed continuous variables) or median [interquartile range (IQR)] for nonnormal quantitative data and frequency (percentage) for categorical data. Data will be evaluated for the presence of outliers, violations of normality, and missing data. Major violations of normality will be corrected with an appropriate transformation procedure (i.e. logarithmic transformation for positively skewed and exponential function for negatively skewed data). To analyse the differences in the continuous variables between the intervention and placebo groups, different tests will be used depending on the data distribution. Paired samples *t*-test will be used for normal data and Wilcoxon signed rank test for non-normal data. Categorical variables will be analysed by *X*^2^ test. Correlations between outcomes will be evaluated by Pearson’s chi-square and Spearman correlation test. Relative risks and weighted mean differences will be employed to calculate the dichotomous and continuous data, respectively.

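### The month-3 values taken just before capsules start have no role in the 12-month comparison, which costs precision but does not cause bias

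*Protocol article*

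**What the plan says.** - **Timing of treatment.** "Intervention (i.e. intake of probiotic or placebo) is administered 3 months after the surgery" (Sample collection and follow-up). Capsules are taken "for 90 days, between 3 and 6 months after bariatric surgery" (Intervention, compliance, and adverse effects). The section on randomization places allocation immediately before the intervention begins, so month 3 is the last untreated time point.
- **Visits.** Participants are seen "at baseline (visit 1), 3 months (visit 2), 6 months (visit 3), 9 months (visit 4), and 12 months (visit 5) after bariatric surgery" (Sample collection and follow-up). Weight is measured and venous blood is drawn at every visit.
- **Weight endpoint.** Under Primary outcomes it is "the number of subjects that will lose at least 50% of excess weight". Under Anthropometry and body composition, "percentage of excess weight loss is calculated as" introduces a formula whose numerator is baseline weight minus follow-up weight. Baseline is visit 1, before surgery.
- **HbA1c endpoint.** It is "the number of subjects that will have glycated haemoglobin levels lower than 5.7%, between the probiotic and placebo groups, 1 year after the surgery", a level rather than a change. Randomisation is stratified by the HbA1c class at visit 1.
- **Analysis.** For continuous variables compared between arms, "different tests will be used depending on the data distribution": a paired t-test or the Wilcoxon signed rank test. Categorical variables get a chi-square test. The only text on adjustment says that potential confounders will be evaluated in each model. It names no month-3 measurement.
- **ClpB, by contrast.** For this secondary marker month 3 is explicitly counted as pre-intervention: "Changes in ClpB levels will be determined before (baseline and 3 months) and after the intervention (6, 9, 12 months".

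**The concern.** During the first three months after surgery neither arm takes capsules, yet the weight lost in that period is part of 12-month %EWL in both arms. Differences between patients in their early response to surgery therefore add variance that the probiotic cannot influence. The same applies to an absolute 12-month HbA1c level. Stratifying on pre-surgery HbA1c class balances the arms on the value before surgery, not on the value at the start of treatment.

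The month-3 weight is a genuine pre-treatment measurement, taken close to allocation and already scheduled. If it predicts month 12, a comparison that ignores it has a wider confidence interval and less power than the same patients could give. With 58 participants planned and 44 counted as evaluable, that information is worth keeping.

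**Working it through.** **Inputs.** From Sample size: SD 10.70 and target difference 10.48 points for %EWL; 44 evaluable participants, so 22 per arm at 1:1. Two-sided 5% is taken as the meaning of 95% confidence. The correlation r between month-3 and month-12 %EWL is **an assumption**, shown from 0.3 to 0.7.

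**The plan's own figure.** The stated 44 does not reproduce. For two independent means, 80% power and two-sided 5%, the t-based requirement is 18 per arm (36 in total) for %EWL and 26 per arm (52) for fasting glucose (11.30 mg/dL, SD 14.00). That is a separate matter. Here 22 per arm serves only as the planned evaluable number.

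**Unadjusted comparison.** An independent-samples t-test stands in for the covariate-free comparison of arms.

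- Standard error = 10.70 × √(2/22) = 3.226.
- Planned effect: 10.48 / 3.226 = 3.248. Noncentral t with 42 df gives power 0.888.
- Half the effect: 5.24 / 3.226 = 1.624, power 0.355.

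**Adjusted for the month-3 value.** Residual SD = 10.70 × √(1 − r²), with 41 df.

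| r (assumed) | Share of variance present before treatment (r²) | Residual SD | Power, 10.48 points | Power, 5.24 points |
|---|---|---|---|---|
| none (unadjusted) | – | 10.70 | 0.888 | 0.355 |
| 0.3 | 9% | 10.21 | 0.914 | 0.383 |
| 0.5 | 25% | 9.27 | 0.956 | 0.449 |
| 0.7 | 49% | 7.64 | 0.993 | 0.603 |

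Adding the HbA1c stratum (three classes, two more df) changes these powers by no more than about 0.001 through the degrees of freedom.

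**Chance imbalance carried forward.** The month-3 difference between arms that arises by chance contributes r × 3.226 to the standard error of the 12-month difference. The 95% range is ±1.96 × r × 3.226, which is ±1.9, ±3.2 and ±4.4 points at r = 0.3, 0.5 and 0.7. This is part of the ordinary sampling error of the unadjusted test, not an addition to it.

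**Room to adjust the responder endpoint.** Assume 80% placebo responders (the Background says that over 20% of patients fall short of 50% at one year), normal %EWL with SD 10.70, and a shift of 10.48 points.

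- Probiotic responders: Φ(0.842 + 10.48/10.70) = 0.966.
- Expected non-responders: 22 × 0.20 + 22 × 0.034 ≈ 5.2 of 44.
- Chance of no non-responder at all in the probiotic arm: 0.9657²² ≈ 0.46.

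Ordinary logistic regression with several covariates would often fail to give finite estimates on such data.

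**The case against.** **Covariates belong in the SAP, and the article leaves room for adjustment.** This stands in part. The choice of covariates is often left to a SAP, and the sentence on confounders does not exclude the month-3 value. But the article goes beyond silence: it fixes the %EWL formula, the stratification visit and a set of tests that take no covariates. Nothing in it gives month-3 weight a role in comparing the arms.

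**A reader might infer that the comparison is biased, or that early weight loss could pass for a probiotic effect.** The documents do not support that. Allocation is randomised, and an unadjusted test already counts chance imbalance in its standard error and type I error. Measuring %EWL from pre-surgery weight also fits an endpoint defined at one year after surgery.

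**A reader might infer that HbA1c is anchored on the pre-surgery value, or that its month-3 value is certainly available.** Neither follows. The endpoint is an absolute level, and baseline HbA1c enters only through stratification. Blood is drawn at all visits, but the text refers to Table 1 for the specific assessments, and that table is not shown.

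**The gain is small where the plan needs it.** This is fair for continuous %EWL at the planned effect, where unadjusted power is already 89%. Half the planned effect is an illustration without a source in the article, and at r = 0.3 the gain there is only three points. However, the stated primary outcomes are responder counts, which use the data less efficiently than the continuous scale on which the sample size was set.

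**Conclusion.** The point holds as a matter of efficiency. The endpoints include change from before treatment, a month-3 weight is measured in every participant seen at that visit, and the stated analysis does not commit to using it. Validity is not affected.

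The gain for continuous %EWL is modest at the planned difference (89% to between 91% and 99%) and larger for a smaller true effect (35% to between 38% and 60% at 5.24 points). These figures rest on SD 10.70, 22 evaluable per arm, a two-sided 5% test and an assumed r of 0.3 to 0.7. A lower r would leave little to gain. The HbA1c part depends on that test being done at visit 2, and the article gives no figure from which to size it.

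**What to change.** - **%EWL.** For the between-arm comparison of continuous 12-month %EWL, prespecify an ANCOVA with treatment arm, month-3 %EWL or weight, and the HbA1c randomisation stratum. A repeated-measures model over visits 3 to 5 with the same covariates is an alternative, and it also uses the data of participants lost after month 6 or 9. Pre-surgery weight may be added. Pre-surgery %EWL may not: by the formula it is 0 for everyone.
- **HbA1c.** Analyse continuous 12-month HbA1c in the same way with its month-3 value, after confirming that it is measured at visit 2.
- **Responder counts.** Keep both primary outcomes as defined. If they are adjusted, use the month-3 value only, with a small-sample method such as Firth's penalised logistic regression, because few participants are expected to miss the weight threshold.
- **Timing.** Fix the covariates before unblinding, so that the choice cannot depend on the results.

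The cost is a short addition to the analysis text and a few degrees of freedom, with little return if r is low. The weight model needs no further visits, measurements or participants.

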### Glycaemic control, lipid profile, and other blood tests

Routine parameters, including fasting blood glucose, insulin, glycated haemoglobin, c-peptide, triacylglycerides, total cholesterol, high-density lipoprotein (HDL) cholesterol, low-density lipoprotein (LDL) cholesterol, very-low-density lipoprotein (VLDL) cholesterol, alanine transaminase, aspartate transaminase, alkaline phosphatase, gamma-glutamyl transpeptidase, vitamins and minerals (iron, calcium, zinc, copper, magnesium, vitamin B6, vitamin B12, 25-hydroxy-vitamin D) are measured by an outsourced certified medical laboratory. Insulin resistance and sensitivity, and β-cell function are estimated by Homeostatic Model Assessment (HOMA) [30]. GLP-1 (Glucagon Like Peptide 1 (Active) ELISA, Merck®, Darmstadt, Germany) and gastric inhibitory polypeptide (GIP) (Human GIP (total) ELISA, Merck®, Darmstadt, Germany) are measured by ELISA procedure.

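### As written, the DPP-IV inhibitor goes into plasma only after the spin, with its amount given per mL of blood, which adds handling noise to the active GLP-1 secondary outcome

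*Protocol article*

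**What the plan says.** The section Sample collection and follow-up describes the steps in order. At every visit "a venous blood sample is collected by a nurse/phlebotomist into sterile serum separator tubes and K_2_EDTA tubes". Then: "Subsequently, blood samples are centrifuged at 3000 rpm for 10 min at 4 °C, and aliquoted". Then, for the incretin aliquot, "DPP-IV inhibitor is added to plasma sample to a final concentration of" 10 μL per mL of blood. No inhibitor is described in the collection tube.

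The section Glycaemic control, lipid profile, and other blood tests names the assay as "GLP-1 (Glucagon Like Peptide 1 (Active) ELISA", whereas GIP is measured as total. Under Secondary outcomes the article states: "GLP-1 and GIP will also be determined at all visits". The Background says that ClpB stimulates secretion of GLP-1 and peptide YY. Of these two hormones, only GLP-1 is listed for measurement.

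**The concern.** Using a DPP-IV inhibitor shows that the authors regard enzymatic loss of the incretins as a threat to the measurement. An inhibitor stops further loss but does not restore what has gone. In the stated order, the sample is unprotected from venepuncture through the spin and aliquoting, and the chosen assay reads the form that is being lost. The measured value then depends on the true level and on how long the tube waited.

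The sentence on the inhibitor also cannot be followed literally. It puts the reagent into plasma but expresses the amount per mL of blood, so two technicians could reasonably add different volumes.

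At stake is the precision of one secondary, mechanistic outcome. Avoidable measurement noise matters in a trial planned on 44 participants before the attrition allowance (Sample size). Drift in handling between visits could also blur the course of GLP-1 over time.

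**Working it through.** No sample size, power or other figure in the plan depends on this step, so there is no stated figure to reproduce. The check has three parts.

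**1. Order of steps (from the text).** Draw into serum separator and K2EDTA tubes, spin for 10 min at 4 °C, aliquot, then add inhibitor to the plasma. The unprotected interval is therefore at least the 10-min spin plus the wait before it and the aliquoting after it.

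**2. Unit conflict.** The input from the article is 10 μL per mL. Haematocrit is assumed to be 40 to 45%, since the article gives none. One mL of blood yields (1 − haematocrit) mL of plasma, so 10 μL per mL of blood, put into the plasma from that blood, is:

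- haematocrit 40%: 10 / 0.60 = 16.7 μL per mL of plasma
- haematocrit 45%: 10 / 0.55 = 18.2 μL per mL of plasma

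Against 10 μL per mL of plasma, the two readings differ 1.67- to 1.82-fold.

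**3. Possible loss and noise (illustration only).** The article gives neither an ex vivo half-life nor a delay, so both are assumed over a wide range. Fraction lost before the inhibitor = 1 − 0.5^(delay / half-life).

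| Assumed half-life | 10 min (spin alone) | 30 min | 60 min |
|---|---|---|---|
| 30 min | 20.6% | 50.0% | 75.0% |
| 60 min | 10.9% | 29.3% | 50.0% |
| 120 min | 5.6% | 15.9% | 29.3% |
| 240 min | 2.8% | 8.3% | 15.9% |
| 480 min | 1.4% | 4.2% | 8.3% |

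The spin is at 4 °C, so the longer half-lives suit that part of the interval better.

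A loss that is the same in every sample scales all values alike and leaves the ratio between arms unchanged. Only variation in delay adds noise. Assume a delay uniform from 15 to 60 min, whose SD is 45 / √12 = 13.0 min. The log-scale SD from handling is then (ln 2 / half-life) × 13.0, which is 0.300, 0.150, 0.075 and 0.038 for half-lives of 30, 60, 120 and 240 min. Assume a between-patient CV of 30% or 50%. The log-scale SD is √ln(1 + CV²), which is √ln(1.09) = 0.294 or √ln(1.25) = 0.472.

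Handling share of variance = handling SD² / (handling SD² + patient SD²). The standardised effect is multiplied by patient SD / √(patient SD² + handling SD²).

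| Assumed half-life | Share of variance, CV 50% to 30% | Effect multiplied by, CV 50% to 30% |
|---|---|---|
| 30 min | 29% to 51% | 0.84 to 0.70 |
| 60 min | 9% to 21% | 0.95 to 0.89 |
| 120 min | 2% to 6% | 0.99 to 0.97 |
| 240 min | 1% to 2% | 1.00 to 0.99 |

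The added noise thus ranges from negligible to substantial, depending on values that the documents do not supply.

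**The case against.** The strongest reply is that the unit points to whole blood. The authors may in fact treat the blood at the draw, and the article may merely misdescribe the step. That possibility stands. It is why the first action is to reconcile the sentence, not to assume a laboratory fault. The text would still need correcting, because its stated order and matrix say otherwise.

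A second reply is that pre-spin cooling and a limit on time to spin belong in a laboratory manual, and that a journal article may leave them out. This also stands, and their absence is no part of the point. The point is the order and the unit that the article does state.

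A third reply is that the stakes are modest. GLP-1 is not a primary outcome, is not named in the specific secondary aims and does not enter the sample size. The trial has one site, random allocation and blinded researchers, so nothing suggests that delay differs by arm. All of this is right and limits the severity.

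A reader might go further and infer that the procedure could create a false treatment effect, that a null GLP-1 result would be uninterpretable, or that values would be pushed below the assay's range. The documents support none of these. Delay independent of arm adds noise and does not bias the ratio between arms. The noise may be trivial. No GLP-1 level or assay limit is given. Nor is any consequence shown for a 1.7- to 1.8-fold difference in inhibitor volume. It is an inconsistency to resolve, not a demonstrated error in results.

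**Conclusion.** The point holds in a limited form. The article's stated sequence leaves active GLP-1 unprotected until after aliquoting, and its inhibitor sentence names one matrix and counts in another. Confidence in both facts is high.

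Confidence in the size of the loss is low: about 50% to 4% for a 30-min delay, at assumed half-lives of 30 to 480 min. The unit conflict is 1.7- to 1.8-fold at the assumed haematocrit of 40 to 45%.

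The expected harm is reduced precision and possible drift between visits in one secondary outcome. Total GIP should be much less sensitive, and the primary outcomes are untouched. Severity is minor to moderate.

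**What to change.** First, reconcile the plasma matrix with the per-mL-of-blood unit in Sample collection and follow-up, and state when the inhibitor is added. If the laboratory already treats whole blood at the draw, a correction of the text is enough.

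If the inhibitor is in fact added after the spin:

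- move the addition to whole blood at the draw, for the tube that supplies the incretin aliquot
- record draw and spin times for each sample
- flag GLP-1 samples collected before the change
- report GLP-1 with and without the flagged samples as a sensitivity analysis.

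The cost is small: the same reagent and tube type, plus a record of times. At the time of writing, 14 of the planned 58 participants had joined (Recruitment status; Sample size), so most samples could still be taken under the changed procedure. The downside is that handling would differ between earlier and later samples, including within some participants, and leaving out flagged samples would remove some baselines. Under blinded randomisation this should fall equally on both arms. That is why the analysis without flagged samples should be a sensitivity analysis and not replace the main one.
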